### Analysis strategy

Results will be reported according to the CONSORT guideline statement [64]. Sociodemographic data at baseline will be presented by means of frequencies (percentages), medians (interquartile range), and means (SD), according to their level of measurement and statistical distribution. Visual inspection on the baseline data will be carried out to check the success of randomization through the two treatment conditions.

The primary efficacy analysis will use an intention-to-treat (ITT) base comparing the main outcome – EPDS – between arms in all the time points as a continuous variable. We will use a repeated measures (RM) design using linear mixed-effects regression models, including participants and the corresponding health center in the random part of the model, by means of the restricted maximum likelihood method (REML). Estimations of slope coefficients (and their 95% confidence intervals [CI]), adjusted for age, nulliparity, previous episodes of depression, and timing of receipt of intervention, will be calculated. To observe the specific trajectories through the study and to evaluate whether possible differences caused by the condition treatment are consistent over time, we will consider the “treatment × time” interaction. In parallel, a per-protocol analysis, with a minimum dose assumed to be ≥ 50% attendance [65], will also be carried out.

If missing data occur in the sample, multiple imputations by using chained equations to replace missing values will be calculated after ensuring data are missing at random (MAR), and as long as there are < 40% missing data in the corresponding variable to ensure validity of imputations [66]. Cohen’s *d* statistic, as an effect size (ES) measure of group differences will be estimated by means of pooled pre-test SDs to weight for the differences in the pre–post means [67]. Values of *d* = 0.20 are regarded as small, 0.50 as medium, and 0.80 large. Secondary analyses will comprise the PSS, PANAS, FFMQ, SCS, and EEP, and will use the same analytical strategy described above.

Cost-effectiveness and cost-utility procedures of analysis will also be conducted calculating incremental cost-effectiveness (ICER) and incremental cost-utility (ICUR) ratios. The effectiveness of the interventions will be estimated by means of the difference between the EPDS score at baseline and at follow-up; utility will be estimated using quality-adjusted life-year (QALYs) at follow-up. QALYs will be calculated using the area-under-the-curve (AUC). In addition, cost-utility planes will be plotted.

The overall alpha level will be set at 0.05 using two-sided tests and considering Benjamini–Hochberg’s correction for the primary outcome analyses as a way to balance between errors. However, no corrections will be made for secondary outcome analyses.

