### Setting and study sample

Participants will be pregnant women in the second trimester of pregnancy living in the city of Valladolid (Spain) who are served by the Spanish NHS. Partners of the expectant women will be encouraged to participate in the courses. Participants considered for inclusion will be: (1) women in weeks 6–25 of pregnancy; (2) able to read, write, and understand Spanish; (3) age ≥ 18 years ; and (4) have signed a written informed consent document following an informed consent procedure. Exclusion criteria will include: (1) any diagnosis of disease that may affect the central nervous system, such as brain pathology or traumatic brain injury; (2) other psychiatric diagnosis or acute psychiatric illness, such as substance dependence or abuse, a history of schizophrenia or other psychotic or eating disorders; (3) any medical, infectious, or degenerative disease that may affect mood; (4) presence of delusional ideas, hallucinations, or at risk for suicide; and (5) currently under psychopharmacological medication or under psychopharmacological treatment.

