### Recruitment

Participants will be recruited from 11 PC urban healthcare centers in the city of Valladolid, Spain through referrals from midwives and obstetricians. When a health provider identifies a pregnant woman who might be a potential participant, they will facilitate contact with the primary study researcher who will arrange a meeting with both the pregnant woman and her partner. During this interview, the study characteristics will be explained, including the main objectives, potential benefits and adverse events, an explanation regarding the assigned home meditation practice, and the option to end their participation in the study at any time. Partners will be encouraged to participate in all of the sessions and the assigned home practices. If a pregnant woman is interested in taking part in the study, the researcher will give her an information booklet with additional details describing the trial. Within three days after having signed the written informed consent form, participants will be interviewed by an independent researcher who will administer the MINI International Neuropsychiatric Interview [46] in order to assess eligibility related to the inclusion and exclusion criteria. If the pregnant woman fulfills all of the study criteria, the same researcher will administer the baseline tests. An independent researcher will conduct the randomization procedure after the baseline assessment. Recruitment will be done consecutively to complete the sample size over an expected 24-month period. Flowcharts giving an overview of the study design and the study timeline are summarized in Figs. 1 and 2, respectively.

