### Interventions

All participants included in the study, whether they receive the adapted MBCP program with compassion practices or not, will be treated by their general practitioner (GP), obstetricians, and midwives according to TAU at a PC level. Women who belong to the same health center will receive the TAU from the same staff. The adapted MBCP program arm will receive a combined treatment, which consists of the MBCP program with compassion practices tailored to the Spanish NHS plus TAU. The program will take place during the second trimester of pregnancy, before participating in the TAU childbirth classes that are taught at their site during the third trimester.

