#### Treatment as usual (TAU)

TAU consists of a childbirth education program that is offered at no charge to pregnant women and their partners by the local midwives in PC facilities in the Spanish NHS. Women usually attend this program in groups of 8–12 couples in the third trimester of pregnancy (during weeks 28–36). It covers basic topics about pregnancy, delivery, postpartum, breastfeeding, and care of a newborn baby. The duration of the TAU course is usually 16 h and includes both information-based classes and some instruction in basic relaxation and breathing techniques to cope with new stressful situations.

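### The primary ITT model adjusts for an undefined timing covariate that, as worded, arises after randomisation and either has no value in the TAU arm or nearly duplicates arm

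*Protocol article*

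**What the plan says.** Under Analysis strategy, the article sets out the main analysis: "The primary efficacy analysis will use an intention-to-treat (ITT) base comparing the main outcome", EPDS, across all time points. The model is a linear mixed model fitted by REML, with participant and health center as random terms. Its coefficients are to be "adjusted for age, nulliparity, previous episodes of depression, and timing of receipt of intervention". Of the time course it says "we will consider the “treatment × time” interaction". The same strategy is applied to the secondary outcomes, including EEP. Multiple imputation is allowed only for a variable with less than 40% of its values missing.

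Other sections fix when things happen:

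- Recruitment: "An independent researcher will conduct the randomization procedure after the baseline assessment".
- Interventions, on MBCP: "The program will take place during the second trimester of pregnancy, before participating in the TAU childbirth classes". Only the MBCP arm receives it.
- Treatment as usual: women usually attend the midwives' course "in the third trimester of pregnancy (during weeks 28–36"). Both arms are offered it.
- Setting and study sample: eligibility covers "women in weeks 6–25 of pregnancy".
- Table 1 and Secondary outcomes list age, nulliparity and previous depression as baseline variables. No timing variable appears there.

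**The concern.** Three of the four covariates are baseline characteristics. The fourth describes when a woman receives something that she can receive only after allocation. An ITT comparison is protected by randomisation as long as the model conditions on variables that allocation cannot influence. Here allocation determines whether the variable exists at all, or which range it falls in.

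The between-arm difference in EPDS at follow-up is therefore at stake. Depending on how the term is coded, that difference could be impossible to estimate, very imprecise, or shifted by whatever links start week to mood within an arm. Because the term is undefined, the coding would be chosen later, possibly with data in hand.

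**Working it through.** The plan gives no figure for this covariate, so each reading of it was worked through with the plan's design inputs: d = 0.59 (outcome SD 1), two-sided tests, local alpha 0.017 and 61 women per arm. With 15% dropout, 61 × 0.85 = 51.85, taken as 51 completers per arm. With no timing term, simulation gives an effect of −0.59, SE 0.20 and power 0.72.

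**Reading 1: timing of MBCP.** TAU women have no value: 61/122 = 50%, above the 40% limit, so the plan's own rule bars imputation. A complete-case fit keeps only MBCP women, and no arm effect, main or interaction, can be estimated.

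**Reading 2: timing of the allocated or first course.**

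- *Coded by trimester* (second for MBCP, third for TAU): the term is an exact function of arm. The treatment coefficient was not estimable in 4000 of 4000 simulated trials.
- *Coded in weeks.* Assumption: start weeks uniform on 14–20 for MBCP (mean 17) and 28–36 for TAU (mean 32).
  - Within-arm variance = (6²/12 + 8²/12)/2 = (3.00 + 5.33)/2 = 4.17.
  - Between-arm variance = ((32 − 17)/2)² = 56.25.
  - Variance inflation = 1 + 56.25/4.17 = 14.5 (simulation: 14.9).
  - SE = 0.197 × √14.9 = 0.76. Simulated power falls from 0.72 to 0.05.
  - If the ranges were less separate and the correlation with arm were only 0.9 (also an assumption), inflation would be 1/(1 − 0.81) = 5.3 and the SE would be multiplied by √5.3 = 2.3.
- *Possible bias.* Suppose start week within the MBCP arm has correlation ρ with distress, and no such correlation exists in TAU. With within-arm SDs of 1.73 and 2.31 weeks, the pooled slope is b = 1.73ρ/(1.73² + 2.31²) = 1.73ρ/8.33, and the adjusted effect is −0.59 + 15b.
  - ρ = +0.1: −0.59 + 0.31 = −0.28.
  - ρ = +0.2: −0.59 + 0.62 = +0.03.
  - ρ = −0.2: −0.59 − 0.62 = −1.21 (simulation: −1.20).

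**Which contrast is hit.** A four-visit REML model was simulated under reading 2 in weeks, with 61 per arm, an assumed intraclass correlation of 0.5 and 150 replicates:

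| Contrast | SE without term | SE with term | Power without | Power with |
|---|---|---|---|---|
| Between-arm, follow-up visits | 0.15 | 0.57 | 0.93 | 0.09 |
| Treatment × time, baseline included | 0.18 | 0.18 | 0.79 | 0.79 |

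With complete data the interaction estimate is identical with and without the term. With 20% dropout it differs by at most 0.016. EEP is measured only at 3 and 6 months, so its overall treatment effect is a between-arm contrast with no baseline visit to fall back on.

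**The alternatives.** With gestational week at inclusion (weeks 6–25) as the covariate, variance inflation is 1.01, the effect −0.59 and power 0.70. With the week of the TAU course used in both arms, and assumed independent of arm and outcome, power is also 0.70.

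**The case against.** The strongest reply is that the term is undefined and may be harmless. It could stand for gestational week at entry, for calendar wave (four MBCP groups over 24 months of recruitment), or for the week of the TAU course that both arms take. Detailed definitions often sit in an SAP. This stands as far as intent goes: the document does not show that a damaging coding was meant. But the words refer to receipt of an intervention and say none of these things. The week of the TAU course, although not fixed by arm, is still set after randomisation.

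A second reply is that the trial is powered on a between-group interaction, and Cohen's d is built on pre–post differences. If inference rests on treatment × time with baseline as a visit, a time-constant covariate hardly matters. This also stands, within limits. The term must enter only as a main effect, and no TAU women may be dropped. It does not cover EEP, nor the between-arm comparison over all time points by which the plan describes its primary analysis; the interaction is introduced there to examine trajectories and consistency over time.

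Two further inferences are tempting but go beyond the text. A reader might conclude that MBCP women who never attend must lack a value; classes run in groups, so the allocated group's dates could be assigned to them. A reader might also take the two week ranges as strictly separate; the plan says only that women usually attend TAU in weeks 28–36.

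**Conclusion.** The concern holds in a conditional form. As worded, the primary model contains a post-randomisation covariate. On one natural reading it has no value in half the sample, beyond the plan's imputation limit, and complete-case fitting removes the control arm. On the other it nearly duplicates arm, so main-effect or per-visit contrasts, including EEP, become imprecise and possibly biased.

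A reader might infer that the trial's treatment effect is bound to be distorted or lost. The documents do not support that: the treatment × time contrast is largely unaffected under the conditions given, and an unstated benign definition is possible. The missing share in the first reading (50% against a 40% limit) follows from the plan's own figures. The variance inflation of 5.3 to about 15, the loss of power and the shifted effects are illustrations. They rest on assumed start weeks, correlations and an intraclass correlation that the document does not give.

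**What to change.** Remove the timing term from the primary and secondary ITT models. If an adjustment for stage of pregnancy is wanted, replace it with gestational week at inclusion, measured before randomisation, and name it among the baseline variables. If that is what was meant all along, saying so is enough. Report MBCP timing descriptively, and explore its relation to outcome only within the MBCP arm, labelled as exploratory.

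The cost is one covariate in the analysis text. Gestational week is already needed to check the weeks 6–25 criterion, so no new data collection or change in trial conduct is required. In the simulation the replacement left the effect and its precision essentially as they were (variance inflation 1.01). The change should be recorded before the outcome data are analysed by arm.

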### Sample size

The sample size estimation was based on the expectation of a moderate standardized mean difference between groups on depressive symptoms at post-birth of *d* = 0.59. Like the protocol that will be used in the present study, this effect size was found in a recent RCT that used a modified MBCP program [24] compared to a TAU active standard childbirth preparation course with no mind–body components. This effect size is also similar to that obtained in other studies using other programs [44], a pilot study evaluating the effectiveness of MBCE [33], a cohort study assessing the MindBabyBody program [34], and a brief pilot adaptation based upon the MBCP program [9]. Considering a statistical power of 80%, a 5% significance level in a between-group interaction with a local alpha of 0.017 in the first test—using Benjamini–Hochberg’s procedure—and a dropout rate in the range of 15%–20%, as has been observed in these types of studies [45], 61 participants are needed in each group, for a total sample size of 122 women.

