### Instruments

All participants included in the trial will be assessed at pre-test/baseline, post- intervention, and at three and six months after childbirth (approximately six and 12 months after inclusion). The study instruments that will be used are summarized in Table 1.

**Table 1 Tab1:** Study instruments

Variable	Area	Type	Time	Application
MINI	Psychiatric disorders	Nominal	Baseline	Researcher A (screening)
Sociodemographic	Age, marital status, education, occupation, nulliparity, and previous episodes of depression	Various	Baseline	Researcher A (baseline)
EPDS	Perinatal depression	Treated as interval	Baseline, post-treatment, and 3-month and 6-month follow-up	Researcher A (baseline) Online (follow-ups)
PSS	Perceived stress	Treated as interval	Baseline, post-treatment, and 3-month and 6-month follow-up	Researcher A (baseline) Online (follow-ups)
PANAS	Positive and negative affectivity	Treated as interval	Baseline, post-treatment, and 3-month and 6-month follow-up	Researcher A (baseline) Online (follow-ups)
FFMQ	Facets of mindfulness	Treated as interval	Baseline, post-treatment, and 3-month and 6-month follow-up	Researcher A (baseline) Online (follow-ups)
SCS	Facets of self-compassion	Treated as interval	Baseline, post-treatment, and 3-month and 6-month follow-up	Researcher A (baseline) Online (follow-ups)
EEP	Satisfaction and self-efficacy feelings about motherhood	Treated as interval	3-month and 6-month follow-up	Online (follow-ups)
CSRI	Use of health and social services	Treated as interval	Baseline and 6-month follow-up	Researcher A (baseline) Online (follow-up)

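### With baseline among its times, the treatment × time interaction shows whether there is any effect, not whether the effect is consistent over time

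*Protocol article*

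**What the plan says.** The Analysis strategy section compares EPDS "between arms in all the time points as a continuous variable" in a repeated-measures linear mixed model with participant and health centre as random effects. Table 1 under Instruments gives the EPDS times as "Baseline, post-treatment, and 3-month and 6-month follow-up". The listed adjustment covariates are age, nulliparity, previous depression and timing of the intervention; baseline EPDS is not among them. On the plain reading, baseline EPDS is therefore an outcome row and baseline is a level of time.

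The same section gives the interaction two purposes. One is to observe trajectories. The other is stated as follows: "to evaluate whether possible differences caused by the condition treatment are consistent over time, we will consider the “treatment × time” interaction". The Sample size section uses an interaction for a different job, as the efficacy test on which the trial is sized: "a 5% significance level in a between-group interaction with a local alpha of 0.017 in the first test", with an expected difference in "depressive symptoms at post-birth of *d* = 0.59". The PSS, PANAS, FFMQ and SCS are measured at the same four times and are to be analysed in the same way.

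**The concern.** The consistency question has a clear null: the arm difference is the same at post-treatment, 3 months and 6 months. An interaction over four visits has another null: the arm difference is the same at all four, baseline included. Since randomisation sets the expected baseline difference to zero, that second null amounts to no effect at any visit. It is false whenever the programme works, whether the benefit holds, grows or fades.

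One term is thus given two readings that do not fit together. Under Sample size, a significant interaction means that the programme works. Under the purpose in Analysis strategy, it would suggest that the effect varies over time. A lasting benefit might be described as time-varying, and a failure to detect any benefit might be described as a consistent effect. The programme is delivered in the second trimester and women are followed to six months after childbirth, so readers will look for exactly this information.

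**Working it through.** **Inputs from the article.** d = 0.59, 61 women per arm, dropout of 15–20%, overall two-sided alpha 0.05, local alpha 0.017, four EPDS times. With 20% dropout, 61 × 0.80 = 48.8, or about 49 per arm.

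**The plan's own figure.** The article gives no figure for the consistency check; the nearest is 61 per group. The usual formula, n = 2(z₁₋α/₂ + z₀.₈₀)²/d², gives 59.9 at two-sided alpha 0.017, so about 60 per arm before any dropout. That is a separate matter. Here it is only the reason to show results for both 61 and 49 per arm.

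**Assumptions.** The article gives no within-woman correlation ρ. I take 0.3, 0.5 and 0.7, under compound symmetry or AR(1), with unit SD. Time is categorical and the interaction is tested globally.

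**Formula.** Let δ be the true arm differences at the visits tested, R the correlation matrix and C the matrix of q between-visit contrasts. The test has a noncentral F distribution with q and 2n − 1 − q degrees of freedom and noncentrality λ = (n/2)(Cδ)′(CRC′)⁻¹(Cδ). Under compound symmetry this reduces to λ = (n/2) Σ(δₜ − δ̄)²/(1 − ρ).

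**Worked case: 61 per arm, ρ = 0.5, compound symmetry, alpha 0.05.**

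- Constant benefit, δ = (0, 0.59, 0.59, 0.59). Σ(δₜ − δ̄)² = 3 × 0.3481 − 4 × 0.4425² = 0.2611. λ = 30.5 × 0.2611/0.5 = 15.93. The four-visit test (3 df) rejects in 92% of trials.
- Benefit that fades to nothing, δ = (0, 0.59, 0.30, 0). Σ = 0.4381 − 4 × 0.2225² = 0.2401. λ = 30.5 × 0.2401/0.5 = 14.64. The four-visit test rejects in 90%.
- Three post-baseline visits only (2 df). For the constant benefit λ = 0, so the test rejects in the nominal 5%. For the fading benefit Σ = 0.4381 − 3 × 0.2967² = 0.1741 and λ = 10.62, so it rejects in 83%.

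Read alone, the global four-visit test cannot separate the two patterns. The post-baseline contrast does.

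**Rejection rate for a constant d = 0.59, four-visit global test, ρ = 0.3–0.7, both correlation structures**

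| Women per arm | Alpha | Range |
|---|---|---|
| 61 | 0.05 | 71–99% |
| 49 | 0.05 | 60–98% |
| 49–61 | 0.017 | 43–98% |

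Simulation with 61 per arm and compound symmetry agrees: 82%, 93% and 99.7% at ρ = 0.3, 0.5 and 0.7 for the four-visit test, and about 5–6% for the post-baseline test.

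**Sensitivity.** A random-intercept model with ρ from 0 to 0.7, 61 per arm and alpha 0.05 gives 33–84% for a constant d = 0.4 and 20–58% for d = 0.3. With time as a straight line, several codings and the same range of ρ, a constant d = 0.59 is flagged in 43–98% of trials with 61 per arm and 36–95% with 49.

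**The case against.** The strongest reply is that the article never says a significant interaction will be taken as inconsistency. It says only that the interaction will be considered, partly to look at trajectories. A reader might infer that the plan will wrongly declare a sustained benefit inconsistent in 60–99% of trials. The text does not support that, because no such rule is written, and the figure depends on an assumed global test, correlation and effect size.

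The second reply is that the text may point to separate contrasts and not to one global test. It promises coefficients with 95% confidence intervals. The local alpha of 0.017 is about 0.05/3, which fits three follow-up-versus-baseline comparisons. Those would distinguish the patterns to a degree. In the worked case the 6-month contrast has standard error √(2/61) = 0.181 and z = 0.59/0.181 = 3.26. It is significant in about 90% of trials at 0.05 (81% at 0.017) if the benefit holds, and in 5% (1.7%) if it has vanished. So it would also be wrong to infer that the planned analysis as a whole cannot reveal a fading effect.

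Third, the form of the test and the coding of time may properly be left to an analysis plan that is not shown, and durability is not the article's stated primary aim.

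These points limit the concern but do not remove it. The article itself assigns the consistency question to the interaction. Whether that term is significant cannot answer the question under either form of test. Several contrasts against baseline, each significant or not, are still not a comparison of the follow-up effects with one another.

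**Conclusion.** The concern holds as a mismatch between a stated question and the tool named for it. It rests on baseline being a level of time, which follows from the wording on time points, Table 1 and the covariate list, but is not spelled out for the interaction. Given that, the structural point needs no assumed correlation: a constant benefit after baseline is an interaction, so significance of the term shows that some effect exists and not that it varies. The size is conditional. For a constant d = 0.59 and a global categorical-time test at alpha 0.05, the false signal of variation would arise in roughly 60–99% of trials under the correlations and numbers per arm assumed above, and less often for smaller effects. Efficacy estimates, sample size and data collection are not affected; what is at risk is the interpretation of durability.

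**What to change.** In Analysis strategy, keep the per-visit (follow-up-versus-baseline) interaction contrasts as the efficacy tests, and say that the interaction including baseline addresses whether there is any effect. Judge consistency only by comparing the three post-baseline arm differences from the same fitted model: a 2-df contrast that they are equal, plus their pairwise differences with 95% confidence intervals. State that a non-significant result will not be read as proof of consistency. Apply the same wording to the PSS, PANAS, FFMQ and SCS. The EEP has no baseline measurement, so the problem does not arise there.

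The cost is one or two sentences and one extra contrast, with no new data or participants. The downside is limited power. For a loss of 0.5 SD between post-treatment and 6 months, taking δ = (0.59, 0.34, 0.09) after baseline, the 2-df contrast detects it in about 35–89% of trials across the same scenarios. The confidence intervals should therefore carry the interpretation.

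### If baseline arm means are left free, the likely EPDS contrast gives up precision that baseline adjustment would recover, and Cohen's d as defined cannot be computed for EEP

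*Protocol article*

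**What the plan says.** In the Protocol article, Analysis strategy, the primary intention-to-treat analysis is described as "comparing the main outcome – EPDS – between arms in all the time points as a continuous variable". It is a linear mixed model fitted by REML with participant and health center as random effects. The covariates named are age, nulliparity, previous episodes of depression and timing of receipt of the intervention. To describe trajectories and the consistency of any difference over time, "we will consider the “treatment × time” interaction". Cohen's d takes differences in pre–post means and scales them by the pooled pre-test SD.

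The Sample size section starts from a "moderate standardized mean difference between groups on depressive symptoms at post-birth of" 0.59, and then refers to "a 5% significance level in a between-group interaction with a local alpha of 0.017 in the first test". The end of the Analysis strategy adds: "The overall alpha level will be set at 0.05 using two-sided tests".

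For the other scales, "Secondary analyses will comprise the PSS, PANAS, FFMQ, SCS, and EEP, and will use the same analytical strategy described above". Table 1 schedules EPDS, PSS, PANAS, FFMQ and SCS at baseline and at three later assessments. It schedules EEP only at three and six months after childbirth.

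**The concern.** Baseline EPDS enters the model as a response, not as a covariate. In the usual form of such a model (arm, time, and arm by time, with a free arm difference at baseline), each interaction coefficient is the between-arm difference in change from baseline. Randomization makes the arms equal at baseline in expectation, so that contrast subtracts a baseline difference that is pure noise. Adjusting for baseline, or giving both arms one baseline mean, removes only as much of it as helps prediction. Main-effect adjustment for previous depression does not recover the loss, because it drops out of a within-person contrast.

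What is at stake is power, and the margin is thin: 61 per arm is about what the stated inputs require before any dropout (see the working).

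The second part needs no assumption. The strategy carried over to EEP includes an effect size that uses a pre-test mean and a pre-test SD, and EEP has neither.

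**Working it through.** **Inputs.** From Sample size: d = 0.59, power 80%, local alpha 0.017, 61 per arm, dropout 15%–20%. From Analysis strategy: two-sided tests. Assumed: the correlation ρ between baseline and follow-up EPDS, which the article does not give; equal SD at each visit (set to 1); no extra variance from health center; completers only.

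**The plan's own figure.** For a comparison of post-scores, n per arm = 2(z₁₋α/₂ + z₁₋β)²/d² = 2(2.387 + 0.842)²/0.59² = 59.9, so 60 per arm; a t-based calculation gives 61.3. Inflating 60 for 15%–20% dropout gives 60/0.85 = 71 to 60/0.80 = 75. The stated 61 therefore matches the calculation before dropout. That mismatch is a separate issue; here it only shows how little slack there is.

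**Which contrast is meant.** Three places point to change from baseline: the sample size uses "a 5% significance level in a between-group interaction", Cohen's d uses pre–post means, and the cost-effectiveness analysis defines effectiveness as the EPDS difference between baseline and follow-up. Against this, Analysis strategy gives the interaction a descriptive purpose, and d = 0.59 is a difference at one post-birth time.

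**Variance per participant for one follow-up visit.**
- Change from baseline: 1 + 1 − 2ρ = 2(1−ρ).
- Baseline-adjusted, or common baseline mean: 1−ρ².
- Ratio: (1−ρ²)/[2(1−ρ)] = (1+ρ)/2, so the saving is (1−ρ)/2.

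The change contrast has the post-score variance of 1, on which d = 0.59 is defined, only at ρ = 0.5.

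**Power** (noncentral t, d = 0.59, two-sided 0.017, 61 × 0.80 = 48.8 per arm):

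| ρ (assumed) | 2(1−ρ) | 1−ρ² | variance saved | power, change | power, adjusted |
|---|---|---|---|---|---|
| 0.3 | 1.40 | 0.91 | 35% | 52% | 73% |
| 0.4 | 1.20 | 0.84 | 30% | 59% | 77% |
| 0.5 | 1.00 | 0.75 | 25% | 69% | 82% |
| 0.6 | 0.80 | 0.64 | 20% | 80% | 89% |
| 0.7 | 0.60 | 0.51 | 15% | 91% | 95% |
| 0.8 | 0.40 | 0.36 | 10% | 98% | 99% |

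**Cross-check.** Generalised least squares for a four-visit model with compound symmetry, with and without a free baseline arm difference, gives the same 30%, 25% and 20% saving at ρ = 0.4, 0.5 and 0.6 for a single visit. For the average of the three follow-ups the saving is 45%, 37.5% and 30%.

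**EEP.** Cohen's d as defined needs a pre-test mean and a pre-test SD. Table 1 has no EEP assessment before three months postpartum, so neither exists. A mixed model over its two visits can still be fitted.

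**The case against.** The strongest reply is that absence from the covariate list does not show that baseline is wasted. Baseline EPDS is among the modelled responses, and a model with a common baseline mean would not list it as a covariate either. If the full plan constrains the baseline means, nothing is lost, and an article may leave that detail to the analysis plan. This stands: the loss is conditional. It does not remove the point, because nothing in the article sets the constraint and the change-based effect size points the other way.

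Some stronger readings are tempting but are not supported:
- **That the interaction is the declared primary contrast.** This is an inference; its stated purpose is trajectories and consistency over time.
- **That the test is biased or invalid.** In a randomized trial the change contrast is unbiased. Only efficiency is at issue.
- **That the loss is a fixed 20%–30%.** That range holds only for ρ of about 0.4–0.6 and one follow-up visit. At ρ = 0.6 the change contrast already has about 80% power after 20% dropout.
- **That ρ must be low because the interval is long.** The last visit is about 12 months after inclusion, but the post-intervention visit is much nearer to baseline. The article does not settle ρ.
- **That time is modelled as linear.** The term slope coefficients may simply mean regression coefficients.
- **That dropout was not considered.** The Sample size section names 15%–20%.
- **That EEP cannot be analysed.** Only its effect size is undefined.

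The power figures also use the 20% end of the dropout range and count completers only. The planned mixed model and imputation would use partial data, so the figures are approximate.

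**Conclusion.** The point holds as a conditional loss of efficiency. If the intended contrast is a difference in change and the baseline arm means are free, a single-visit comparison has a variance larger than necessary. Adjustment would remove 35% of it at ρ = 0.3, 25% at 0.5 and 10% at 0.8. In power, after 20% dropout, the gain is about 21 percentage points at ρ = 0.3 (52% to 73%), 13 to 14 at ρ = 0.5 (69% to 82%) and 4 at ρ = 0.7 (91% to 95%). The direction is certain for any ρ below 1; the size depends on a ρ that the article does not report.

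The EEP part is a plain internal contradiction, limited to the effect size of one secondary outcome.

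**What to change.** State how baseline EPDS is handled, by one of two routes and not both:
1. Keep baseline as a response, with time categorical and a common baseline mean across arms.
2. Model only the post-baseline EPDS, with baseline EPDS and baseline by time as covariates.

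Name the adjusted between-arm difference at each follow-up visit as the reported treatment effect. Do the same for PSS, PANAS, FFMQ and SCS. For EEP, compare arms at three and six months and standardise by the pooled SD at that visit.

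The cost is analysis wording only. Every measurement needed is already in the Table 1 schedule, and neither sample size nor conduct changes.
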